### Subacromial decompression surgery

Subacromial decompression surgery is performed under general anesthetic. The procedure involves insertion of an arthroscope into the glenohumeral joint where the joint surface is inspected along with the intra-articular portion of the long head of the biceps and the joint surface of the rotator cuff tendons. Once this has been performed the arthroscope is removed and inserted into the subacromial bursa, which lies outside the rotator cuff tendons and beneath the acromion process of the scapula. In the bursa, the acromion and superior surface of the rotator cuff are assessed to ensure the coracoacromial ligament and the Acromioclavicular (AC) joint remains intact. The projecting under surface of the distal part of the acromion is resected. The intervention is considered to be a well-established and well-documented procedure. Patients with full cuff tears noted at the time of surgery will not be eligible and will be excluded from the trial at operation.

### Subacromial decompression surgery with autologous platelet-rich plasma

This group will receive the same operation as described above plus an autologous platelet-rich plasma concentrate injection into the rotator cuff tendon during surgery. PRP can be applied by a variety of methods: as a gel, as an injection, as a sutured film during surgery, sprayed directly onto repaired tissue or injected subcutaneously. This study proposes the use of a gel sprayed directly onto the decompression area.

Specific preparation techniques will be stipulated by the company providing the PRP device. Described below is a guideline for the preparation involved in administering PRP, which was taken from the protocol of the PATH study (REC Reference: 09/H0605/78), also run in this department.

PRP is prepared using a sterile technique in the theatre. First, 50 ml of venous blood will be withdrawn from the patient into a syringe. The syringe will be attached to the selective platelet separator device and the blood is transferred into the device. The device will separate platelets and remove red blood cells and white blood cells. The result is 5 ml to 6 ml of platelet-rich concentrate (PRC), which will be collected in an attached syringe [13].

The 5-ml syringe containing the concentrate is attached via a dual injection kit to another syringe containing bovine thrombin (200 units) and 1 ml of 10% calcium chloride (activator). The dual syringes are used to inject the PRC into the subacromial space.

Reviews in oral surgery recommend that the derivation of PRP must be a sterile process. Platelets must not be lysed or damaged in any way, as damaged platelets may not release their growth factors. Studies that suggest there is no benefit to PRP application may have suffered from poor preparation of the PRP solution [14]. It is therefore important to send excess PRP to the laboratory for platelet analyses and quality assessment [15]. Data obtained from tendon tissue samples from all patients will also provide valuable information regarding the integrity of the tendon including any effects PRP may have on this.

### Tendon biopsies

Tendon biopsies for histological assessments will be taken during surgery for both groups of patients. This will involve a small amount of tendon tissue (the size of a small grain of rice) excised using a 14G core biopsy needle under ultrasound guidance. This will be taken in a sterile manner as part of the surgical procedure before the application of the PRP.

A further biopsy will be taken from both groups of patients during their 3-month follow-up visit. This biopsy will be taken using an ultrasound guidance technique and a biopsy needle in exactly the same manner as performed at surgery, under sterile conditions. Local anesthetic will be infiltrated around the area of the biopsy to numb the region before the tissue sample is taken. This technique has been successfully trialed and used in previous studies conducted by this research group (ethics ref: 09/H0605/111 and 09/0605/78).

### Venous blood sampling

A sample of 18 ml of venous blood will be obtained from the patient for analysis and inclusion in the Oxford Musculoskeletal BioBank project (ethics ref: 09/H606/11). The sample will be taken prior to commencement of surgery once the patient is anesthetized. For those patients in the PRP group this sample will be taken using the same needle as for the blood taken for making up the PRP solution. In this way patients will be blinded to their group allocation as both groups will have a single venepuncture site and the sampling volume will be unknown to the patient as they will have been anesthetized prior to venepuncture.

### Safety

Adverse events have not been reported well in previous studies involving PRP. This study will record expected adverse events and will report unexpected events that are related to the patients’ participation in the study. PARot’s final report will include a section on adverse events even if this is just to confirm that none were reported.

### Statistics and analysis

The planned study examines a continuous response variable (OSS) from independent control and experimental subjects. In previous studies the response within each subject group was found to be normally distributed with a standard deviation of 3 points. If the true difference (or the meaningful clinical difference) in the experimental and control means were 3 points on the OSS, we would need to study 17 experimental subjects and 17 control subjects to be able to reject the null hypothesis that the population means of the experimental and control groups are equal with probability (power) 0.8. The Type I error probability associated with this test of this null hypothesis is 0.05 (α). To allow for losses to follow-up we aim to recruit 20 patients in each arm.

### Analysis of endpoints

Reporting of outcomes will follow CONSORT Guidelines. Full details of the planned analysis will be detailed in the statistical analysis plan and approved by the trial team prior to any analysis being undertaken.

### The Oxford shoulder score

The OSS at 12 months is the primary outcome measure and the primary hypothesis is based upon this evaluation. The design is a simple two-group cross-sectional comparison. The data will be first checked for normality using histograms and Shapiro–Wilk tests. Independent *t*-tests (assuming normal distribution and equal variance) will then be performed to test the hypothesis that there is no difference in the mean OSS between the two groups. The null hypothesis will be rejected for significance set at α = 0.05.

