## Methods/design

PARot is a parallel blinded superiority-type randomized controlled trial. The two groups are: arthroscopic subacromial decompression surgery and arthroscopic subacromial decompression surgery with application of PRP.

The study will run for 3 years. Recruitment will be for 24 months with final follow-up at 1 year post surgery. The final year will involve collation and analysis of the data. Only patients will be blinded as to whether they received PRP or not.

Patients identified for the study will have failed conservative treatment for their shoulder impingement or partial-thickness tear and will be listed for subacromial decompression surgery. Conservative treatment may include physiotherapy and injections of steroid and or local anesthetic. The routine step following failed conservative treatment would usually involve being put on the waiting list for surgery (SAD).

Patients will be identified in, and recruited from, the shoulder outpatient clinics at the Nuffield Orthopaedic Centre, Oxford University Hospitals (OUH) NHS Trust, Oxford. Diagnosis of shoulder impingement or partial-thickness tear will be confirmed with ultrasound in the clinic and the patient will be put on the waiting list for surgery. A surgical member of the research team will introduce the trial to the patient and refer them to a research nurse for recruitment.

Informed consent procedures, baseline assessments (including the Oxford shoulder score) and randomization are performed up to 3 days prior to surgery due to organizational requirements in relation to operating schedules and required equipment. Randomization is undertaken using sealed envelopes based on a simple computer-generated randomization list.

Routine perioperative care will proceed and the patient will have their operation as planned.

As randomization occurs very close to the point of treatment, patients will be followed up in clinic at 6 weeks and at 3 and 6 months post treatment. Patients will be blinded to the treatment they are allocated to. Assessors and surgeons are unable to be blinded in this instance. All patients will remain on the waiting list for surgery as per standard care and may have their surgery at the planned date. A summary of the study design is portrayed in the flow chart (Figure 1).

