**Figure 1 F1:**
[figure not shown]
**Study flow chart.** PROMS, patient-reported outcome measures.

PARot study assessments will include patient-reported outcome measures (PROMs), histological examinations, functional assessments and patient satisfaction and health economic questions. Evaluation of routine basic blood tests will also be included in the PARot assessments. A full blood count (taken as part of routine preoperative assessment and not a study intervention) will indicate the presence of clotting substances and any PRP contraindications the patient may have.

Patients will be required to attend a clinic appointment for assessments at 6 weeks and at 3 and 6 months post treatment. A postal questionnaire (containing the Oxford shoulder score, Oxford satisfaction index and EQ 5D) will also be sent out at 12 months post treatment. Clinical assessments and any adverse reactions or side effects can be documented. Table 1 outlines the outcome measures and their correlating time points.

**Table 1 T1:** Outcome assessments

	**Baseline**	**6 weeks**	**3 months**	**6 months**	**12 months**
**Oxford shoulder score**	X	X	X	X	X
**Tissue biopsy**	X^a^		X^b^		
**Pain diary**		X			
**Clinical examination**	X	X	X	X	
**Oxford satisfaction index**	X	X	X	X	X
**EQ 5D**	X	X	X	X	X
**Complications**	X	X	X	X	X
**Venous blood sampling**	X				
**Ultrasound**	X		X	X	

^a^ Ultrasound-guided biopsy during surgery.

^b^ Ultrasound-guided biopsy at follow-up visit.

The primary outcome measures are the Oxford shoulder score (OSS) assessed at 12 months and the histological assessments of the biopsy tissue. The Oxford shoulder score is a condition-specific questionnaire providing a total score based on the patient’s subjective assessment of pain and activities of daily living (ADL) impairment. The range of available scores is 0 (worst) to 48 (best) [11]. The score is reliable and valid. The questionnaire will be administered to patients at the baseline and during their follow-up visits.

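### The primary t-test on 12-month OSS leaves out the baseline OSS that is collected; the test is valid, but baseline-adjusted ANCOVA would be more precise unless the baseline to 12-month correlation is very low

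*Protocol article*

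**What the plan says.** Under The Oxford shoulder score, the protocol article states that "The OSS at 12 months is the primary outcome measure and the primary hypothesis is based upon this evaluation" and then fixes the comparison: "The design is a simple two-group cross-sectional comparison". The test is an independent t-test, "assuming normal distribution and equal variance) will then be performed to test the hypothesis that there is no difference in the mean OSS" between the groups. The article mentions no baseline covariate, change score or repeated-measures model.

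The baseline score exists. Methods/design says that "baseline assessments (including the Oxford shoulder score) and randomization are performed up to 3 days prior to surgery". Table 1 marks the OSS at baseline, and the text below it adds that "The questionnaire will be administered to patients at the baseline and during their follow-up visits".

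Allocation does not balance the score: "Randomization is undertaken using sealed envelopes based on a simple computer-generated randomization list". No stratification or minimization is described.

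Statistics and analysis sizes the trial on the same unadjusted comparison: difference 3 points, SD 3 points, alpha 0.05, power 0.8, 17 per arm, raised to 20 per arm for losses. Analysis of endpoints leaves full details to a statistical analysis plan, to be approved before any analysis.

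**The concern.** The baseline score is the same instrument as the primary outcome and is part of the baseline assessments, so the information is already paid for. In a trial of about 40 patients it can help in two linked ways.

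- **Precision.** If baseline OSS predicts 12-month OSS with correlation r, adjustment multiplies the residual variance by about 1 − r². The treatment effect being estimated is unchanged.
- **Chance imbalance.** With a simple list and 17 to 20 patients per arm, baseline means can differ by chance. The unadjusted estimate keeps the part of that difference which persists to 12 months.

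These are two views of the same variance and should not be counted as separate gains. At stake is a wider confidence interval than the data need. There is also a practical risk: if the arms differ visibly at baseline, an adjustment added after the data are seen would look selective.

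**Working it through.** **Inputs from the article (Statistics and analysis):** difference δ = 3, SD σ = 3, α = 0.05, power 0.8, n = 17 per arm, 20 per arm recruited. Sidedness is not stated.

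**Assumptions:** two-sided test; baseline SD equal to the 12-month SD; r not given, so taken from 0 to 0.7.

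**1. The plan's own figure.** Noncentral t with df = 2n − 2 and noncentrality δ / (σ√(2/n)). At n = 17 this is 3 / (3 × √(2/17)) = 1/0.343 = 2.92, and power is 0.807. At n = 16 power is 0.781. So 17 per arm is reproduced with a two-sided test. A one-sided test by the normal approximation would need 13. The recruitment target follows from 15% loss: 17/0.85 = 20.

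**2. Power with ANCOVA at 17 per arm.** The simple formula uses residual SD = 3√(1 − r²) and df = 31. It leaves out the cost of estimating the baseline slope from 34 patients, which raises the variance of the adjusted difference by about 1/30 on average. Simulating the full ANCOVA (200,000 trials for each r) includes that cost.

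| r | Variance removed (r²) | Power, simple formula | Power, simulated ANCOVA |
|---|---|---|---|
| 0 | 0% | 0.806 | 0.79 |
| 0.2 | 4% | 0.822 | 0.81 |
| 0.3 | 9% | 0.841 | 0.83 |
| 0.5 | 25% | 0.903 | 0.89 |
| 0.7 | 49% | 0.977 | 0.97 |

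The unadjusted test gives 0.807 throughout. The simulated column is the one to rely on. ANCOVA breaks even at about r = 0.2: setting (1 − r²)(1 + 1/30) = 1 gives r² = 1/31, so r = 0.18.

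**3. How often baseline means differ.** The standard error of the baseline mean difference, in SD units, is √(2/n): 0.316 at 20 per arm and 0.343 at 17. The chance of a gap above g SD is 2(1 − Φ(g/√(2/n))).

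| Gap | 20 per arm | 17 per arm |
|---|---|---|
| above 0.3 SD | 34% | 38% |
| above 0.5 SD | 11% | 14% |

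**4. What such a gap does to the estimate.** With equal SDs the shift is r × gap. A 0.5 SD gap is 0.5 × 3 = 1.5 points. It moves the unadjusted estimate by 0.3 × 1.5 = 0.45 points at r = 0.3, 0.5 × 1.5 = 0.75 at r = 0.5, and 0.7 × 1.5 = 1.05 at r = 0.7. The planned difference is 3 points.

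**The case against.** The strongest reply is that nothing here is incorrect. Under randomization the t-test is unbiased and controls type I error, it matches the sample-size calculation, and it reaches the stated power. Chance imbalance is already part of the sampling variance that its standard error reflects. All of this stands. The point is therefore about efficiency and prespecification.

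A reader might infer more, and the documents do not support it:

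- *That the trial is underpowered because of this choice.* It is not, on its own inputs. Power is lost only relative to ANCOVA.
- *That a baseline gap passes in full into the result.* Only the fraction given by the baseline-outcome slope does.
- *That a large imbalance is likely.* A gap above 0.5 SD has an 11% chance at 20 per arm, and even a gap above 0.3 SD is absent in about two trials out of three.
- *That adjustment is free.* At r = 0 it costs about 1 to 2 power points, and the article excludes no value of r.

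The deferral to a statistical analysis plan is only a partial answer. The article itself names the design, the test, its assumptions and the significance level, so a plan that specified ANCOVA would have to be reconciled with it.

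Timing is a fair objection. Trial status reports completed follow-up on 40 patients, the full target, and assessors and surgeons are not blinded. Changing the primary test after outcomes have been compared by arm could look data-driven. This limits when the change can be made, and does not defend the t-test itself.

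**Conclusion.** The point holds as a recommended improvement. The article fixes a valid but less precise primary analysis while collecting the covariate that would sharpen it. At 17 per arm the change in power from ANCOVA runs from a loss of 1 to 2 points at r = 0, through no material difference at r = 0.2, to gains of about 2 points at r = 0.3, 9 at r = 0.5 and 17 at r = 0.7.

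The direction is secure for r above about 0.2. The size is not, because it depends on a correlation that the article does not report. The figures also assume the planned SD of 3, equal SDs at both times and a two-sided test.

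**What to change.** In The Oxford shoulder score section and in the statistical analysis plan, make the primary analysis an ANCOVA of 12-month OSS on treatment group with baseline OSS as covariate. Report the adjusted mean difference with its 95% confidence interval, tested at two-sided 0.05. Keep the unadjusted t-test as a sensitivity analysis.

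Make and date the change before any comparison of outcomes by arm, and record that none had been made. The article's rule that the analysis plan is approved before analysis gives the route. If outcomes have already been compared by arm, keep the published t-test as primary and report the ANCOVA as a supporting analysis, labelled as such.

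The cost is a short amendment, one degree of freedom (32 to 31 with 34 patients) and the small power loss shown above if r is near zero. No new data are needed and the sample size can stay as it is.

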### Histology assessments

The tendon structure will be examined with basic histology by staining specimens with hematoxylin and eosin, toluidine blue and Congo red. Immunohistochemical analysis will also be performed using specific antibody markers such as vascular endothelial markers (CD 34), macrophage-associated markers (CD 68) [12] as well as neural tissue (S100) and cell proliferation (PCNA). Statistical analysis with *t*-tests will be used with significance set at α = 0.05.

### Secondary outcome measures

Descriptive statistics will be presented for the secondary endpoints but no formal significance tests will be performed. The sample size is insufficient to test hypotheses for this categorical data but some valuable indication of effect may be observed.

### Ethics

The study has obtained approval from the National Research Ethics Service, Oxfordshire, REC C in October 2010 (0/H0G0OIO0).

## Trial status

The trial is currently recruiting patients and has completed follow-up on 40 patients.

## Abbreviations

ADL: Activities of daily living; NHS: National Health Service; NIHR: National Institute of Health Research; OSIRIS: Orthopaedic Surgical and Interventional Research Group; OSS: Oxford shoulder score; OUH: Oxford University Hospitals; PROMS: Patient-reported outcome measures; PRC: Platelet-rich concentrate; PRP: Platelet-rich plasma; PTT: Partial-thickness tear; SAD: Subacromial decompression; AC joint: Acromioclavicular joint; USS: Ultrasound scan; BRU: Biomedical Research Unit.
